## Abstract

**Background:** Hypertension is one of the most important risk factors for stroke and heart disease. Recent international guidelines have stated that
*'poor adherence to treatment – in addition to physician inertia - is the most important cause of poor blood pressure control'.* The MaxImising Adherence, Minimising Inertia (MIAMI) intervention, which has been developed using a systematic, theoretical, user-centred approach, aims to support general practitioners (GPs) and people with hypertension to maximise medication use, through the facilitation of adequate information exchange within consultations about long-term antihypertensive medication use and adherence skill development. The aim of the MIAMI pilot cluster randomised controlled trial (RCT) is to gather and analyse feasibility data to allow us to (1) refine the intervention, and (2) determine the feasibility of a definitive RCT.

**Methods:** GP practices (n = 6) will be recruited and randomised to the intervention arm (n = 3) or usual care control arm (n = 3). Each practice will recruit 10 patient participants. For a patient to be eligible they must have a diagnosis of hypertension, be on two or more anti-hypertensive medications, must not be achieving recommended blood pressure levels, and be over the age of 65 years. Participants in the intervention arm will meet their GP and receive the MIAMI intervention twice over three months. Quantitative data collection will take place at baseline and three month follow up. A pilot health economic analysis and a qualitative sub-study will also be incorporated into the study.

**Discussion:** This pilot cluster RCT of the MIAMI intervention will allow us to gather valuable acceptability and feasibility data to further refine the intervention so it optimally designed for both GP and patient use. In particular, the qualitative component will provide an insight into GP and patient experiences of using the intervention.

## Introduction

Hypertension is one of the most important risk factors for stroke and heart disease
^
1
^. A landmark study of twelve high income countries from 1976–2017 concluded that hypertension ‘
*control rates have plateaued in the past decade, at levels lower than those in high quality hypertension programmes*’
^
1
^. International comparisons suggests that in Ireland there are relatively low levels of awareness of hypertension and relatively poor levels of control and suboptimal treatment. For example, estimates from the same international study indicate that the proportion of Irish male patients with controlled blood pressure is 17%, while the comparable figure in Canada is 69%
^
1
^. A parallel paper reviewing the state of hypertension care for 1.1 million adults in 44 low- and middle-income countries
^
2
^ identified countries in each world region that performed better than expected from their economic development. Many of these countries, which spend much less on healthcare than Ireland, significantly outperformed Ireland in hypertension awareness, treatment and control.

Recent international guidelines have stated that
*'poor adherence to treatment – in addition to physician inertia - is the most important cause of poor blood pressure (BP) control'*
^
3
^. The adverse impact of poor adherence to anti-hypertensive medication has been recently shown in a Korean study
^
4
^. This showed, in a random sample of 33,728 patients with hypertension, that poor medication adherence was associated with higher mortality and the development of key negative cardiovascular outcomes. For example, patients with poor medication adherence had, in comparison to those with good adherence, worse ischaemic heart disease mortality (hazard ratio [HR] 1.64; 95% confidence interval [CI] 1.16-2.31) and cerebral haemorrhage (HR 2.19; 95% CI 1.28-3.77). Improving adherence to antihypertensive medication has the potential to quickly lower blood pressure and to reduce the related cardiovascular risk in most patients
^
3
^. Gupta and colleagues in a non-randomised study of 238 UK patients with apparent resistant hypertension (high blood pressure that is not responsive to treatment) attending a tertiary referral centre utilised sequential biochemical urine screening for assessment of adherence
^
5
^. The results of this testing were fed back to patients, with subsequent significant improvements in both adherence and blood pressure (systolic 32.6mmHg and diastolic 7.5mmHg). This approach, referred to as chemical adherence testing, may have some potential to enhance collaboration between patients and physicians in optimising the management of hypertension
^
6
^.

Clinical inertia is largely seen as failure to advance therapy when appropriate to do so, and this is particularly relevant in the treatment of hypertension. Two Irish studies have confirmed that suboptimal dosing is a significant issue in Irish general practice populations of patients with resistant hypertension
^
7
^ and post stroke and/or transient ischaemic attack
^
8
^. In 646 patients with apparent resistant hypertension from 16 independent centres, i.e., community-based general practice sites, 19% of patients had adequate dosing for each hypertensive medication according to the World Health Organisation defined daily dose guidelines
^
9
^. However, in terms of the definition of ‘clinical inertia,’ it can be argued that failure to advance therapy when indicated is just one facet of a larger phenomenon. Khunti and Davis argue that ‘clinical inertia’ is not only related to escalation of therapy but is a much wider concept and encompasses failure to improve care at many levels of health care
^
10
^. In the context of hypertension care, we know that conversations around medication adherence are often avoided. A recent survey of 200 hypertension specialists in 30 countries found that the topic of medication taking was under attended to, despite its importance
^
11
^. A similar survey of healthcare professionals (n = 3196) working in primary care in Europe found that less than half of respondents ever asked their patients whether they have missed any doses of their medication
^
12
^. It can be argued, therefore, that tackling clinical inertia in hypertension care involves addressing issues of medication adherence as well as optimal dosing.

The ‘MaxImising Adherence, Minimising Inertia’ (MIAMI) intervention, which has been developed using a systematic, theoretical, user-centred approach, aims to support GPs and people with hypertension to maximise medication use. The Behaviour Change Wheel (BCW)
^
13
^ and Collective Intelligence (CI) methodology
^
14
^ were used in development and a detailed description of the process will be described elsewhere. In brief, we used evidence developed by the team
^
7,
15–
18
^, along with Public and Patient Involvement (PPI) input, to inform Phase 1 of the BCW, ‘understanding the behaviour’. We then operationalised Phase 2 ‘identifying intervention options’ and Phase 3 ‘identifying content and implementation options’ through a CI workshop. Workshop attendees included people with backgrounds in GP, nursing, pharmacy, clinical pharmacology, health psychology, PPI contributors and lay people. Scenario-based design (informed by Phase 1 and relevant theory
^
19,
20
^) was used to generate user needs, from both the GP and patient perspective. The outputs of the workshop were refined with guidance from the PPI panel. A full description of the intervention can be seen in
Table 2. The MIAMI intervention specifically targets older patients (over 65 years of age), as they are at increased risk from both hypertension
^
3
^ and medication non-adherence, given the increased likelihood of multimorbidity and the related challenge of polypharmacy in older adulthood
^
21,
22
^.

### Aims of the MIAMI cluster pilot RCT

The aim of the MIAMI pilot cluster randomised controlled trial (RCT) is to gather and analyse feasibility data to allow us to (1) refine the MIAMI intervention, and (2) determine the feasibility of a definitive RCT.

Specifically, the MIAMI pilot cluster RCT has the following objectives:

1.To investigate if the MIAMI intervention is acceptable to GPs and people with hypertension;2.To assess the feasibility of recruitment and retention of both practices and patients;3. To assess the feasibility of outcomes and measures used;4.To conduct a pilot health economic assessment of the MIAMI intervention;5.To inform the sample size calculation, including the optimal number of GP practices (clusters) and people with hypertension (participants), for a definitive cluster RCT;6.To assess the feasibility of a ‘Study Within A Trial’ focused on the impact of an informational video on study retention levels

This protocol has been registered on ISRCTN (registration number: ISRCTN85009436) and all study materials can be found as
*Extended data*
^
23
^.

### Design

This is a pilot cluster RCT with an intervention arm and a control arm. The intervention arm is the MIAMI intervention and the control arm is usual care.

### Inclusion and exclusion criteria

Please see
Table 1 for inclusion and exclusion criteria.

**Table 1. T1:** Inclusion and exclusion criteria.

Inclusion criteria for GP practices	Inclusion criteria for GP participants	Inclusion criteria for patient participants
• Within catchment area of biochemistry lab at University Hospital Galway • Use Socrates software system	• Doctors who are providing patient care in the practice	• A confirmed diagnosis of hypertension • Participants must be over the age of 65 • Participants must be on two or more anti- hypertensive medications • Participants must not be achieving recommended blood pressure levels, i.e., clinic readings are higher than 140/90 mmHg or day ABPM 135/ 85 mmHg • In the judgement of the GP regarding a change in medication, the balance of risk / benefit lies in favour of benefit.
		**Exclusion criteria for patient participants**
		• Inability to give informed consent • Resident in a nursing home • Currently attending a hospital resistant hypertension clinic

**Table 2. T2:** MIAMI intervention.

GP intervention components		
Component	Details	Timing of delivery
Training videos	30 minute training (6 short videos and quiz) Part 1: Adherence to medication, including the extent of non-adherence, key factors associated with adherence, and types of non-adherence Part 2: Three case studies to illustrate how you might support patients’ medication adherence in different scenarios Part 3: Skills and strategies to support adherence Part 4: A case study illustrating the use of the MIAMI intervention	Beginning of study, before meeting any patient participants
MIAMI booklet	Booklet contains • Blood pressure thresholds (American College of Cardiology) • Oral anti-hypertensive drugs (American College of Cardiology) • Core drug treatment strategy for uncomplicated hypertension (European College of Cardiology) • List of available single pill combinations • Simple reiteration of key training messages	Beginning of study, before meeting any patient participants
Drop down menu on computer to guide consultation* * *All GP practices in this study will be * *using Socrates software. Dropdown * *menus are easily integrated into this * *software and will be done by the * *research team prior to study beginning.*	Drop down menu on computer which contains a guide to the consultation. • Discussed ABPM YES/NO • Discussed urine results YES/NO • Made an agreed plan which may include: single pill combinations, ‘blister pack’ specification: YES/NO • Asked patient to form a habit (pair medication taking with another stable behaviour e.g. a mealtime/brushing teeth/ Coronation Street): YES/NO • Wrote out the agreed plan on the ‘MIAMI pre-consultation tool’ YES/NP • Sent relevant text message: YES/NO Text to copy and paste into text messages You can set up text messages to remind you to take your medication at dontforget.ie Information about blood pressure and blood pressure medication is available on the Croí website https://croi.ie/health/heart-conditions/ high-blood-pressure/	Set up prior to study beginning. To be used during consultations.
**Patient intervention components**		
**Component**	**Details**	**Timing of delivery**
Pre-consultation plan	Short document containing • ‘What do you want to talk about at your blood pressure appointment today’ (to be filled in prior to consultation) • Textbox for BP reading and whether it is in target • Textbox for goal setting and action planning (to be used during consultation)	Given at practice visit 2, prior to GP consultation. To be used at the beginning and during the consultation. This is optional and patient participants can decide whether or not they want to use it.
GP consultation	Discussion of ABPM and urine test results. Use of pre-consultation plan to create shared action plan GP to review prescription and adjust to include single pill combinations and blister pack if appropriate GP to advise on habit creation GP to send text messages on dontforget.ie and Croí website if appropriate	GP consultation
Croí website	Page on website containing (both text and video format) • information on BP • BP values • how medication works • benefits of medication possible side effects	GP to recommend to patient during consultation

### Sample size calculations

As this is a pilot study, a formal sample size calculation is not warranted. One of the aims of the study is to generate the estimates needed for a sample size calculation for a future definitive trial. In order to generate the reliable estimates needed, it is proposed that six clusters (three in the intervention arm, three in the control arm) each containing 10 patient participants are recruited. Each cluster will be an independent GP practice, meeting the inclusion criteria laid out in
Table 1. The number of clusters chosen is governed by pragmatism and to provide a representative sample (using best judgement) of the diversity in the population of clusters from which data in the definitive trial will be sampled. 

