### Statistical analysis

Suitable summary statistics (e.g., mean, standard deviation, and frequency) will be provided for the main outcomes. These summary statistics will guide the sample size calculation needed for the future definitive two arm cluster RCT
^
37,
38
^.

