### Progression to a full RCT

The following pre-defined stop/go criteria in
Table 4 will be used to inform the decision on whether to proceed to a full trial.

**Table 4. T4:** Stop/go criteria.

	Go – proceed with full RCT	Amend – proceed to full RCT with changes	Stop – do not proceed unless major changes are possible
1. Feasibility of practice recruitment Can 6 practices be recruited to take part in 3 months?	If ≥5 practices are recruited to take part in 3 months	If ≥5 practices are recruited, but it takes longer than predicted (e.g. 3–6 months)	Unable to recruit at least 4 practices.
2. Feasibility of patient recruitment Can 10 patients per practice (total n = 60) be recruited?	If 8–10 patients are recruited in one month per practice: total of 60 (100%)	If 6-7 patients are recruited in one month per practice: total of 36–60 (60% to ≤100%)	If <6 patients are recruited in one month per practice: total of ≤36 (<60%)
3. Feasibility of practice retention Can all 6 practices be retained in the study until completion?	≥5 retained	≥4 retained	≤3 retained
4. Feasibility of patient retention * Can at least 90% of recruited patients be retained in the study until completion?	>9 patients (90%) retained	7–8 patients (70-80%) retained	<7 patients (<70%) retained
5. Intervention feasibility	Delivery of intervention judged strongly feasible by qualitative data	Delivery of intervention judged mainly feasible by qualitative data	Delivery of intervention judged problematic by qualitative data

**Retention will be defined as availability of final outcome measures*.

The Decision-making after Pilot and feasibility Trials (ADePT) process involves examining 14 methodological issues that are pertinent to feasibility research. We will use this process, as well as the progression criteria, findings from the qualitative research, and discussions with the study research team, Trial Management Group, Trial Steering Committee and the public and patient involvement (PPI) panel to make a decision on whether to progress to full RCT.

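### Six practices of ten patients cannot give a reliable estimate of between-practice variance, although the protocol says they will yield the reliable estimates needed to size the definitive cluster trial

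*Protocol article*

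**What the plan says.** The Sample size calculations section of the protocol article opens by saying "As this is a pilot study, a formal sample size calculation is not warranted". It then gives the purpose of the chosen size: "it is proposed that six clusters (three in the intervention arm, three in the control arm"), "each containing 10 patient participants are recruited", and the stated reason is to produce the reliable estimates that the definitive sample size needs ("In order to generate the reliable estimates needed, it is proposed that six clusters"). The same paragraph explains the choice of six differently: "The number of clusters chosen is governed by pragmatism and to provide a representative sample (using best judgement"). It gives no precision target.

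Objective 5, in the Aims section, is "To inform the sample size calculation, including the optimal number of GP practices (clusters) and people with hypertension (participants), for a definitive cluster RCT".

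The Statistical analysis section gives mean, standard deviation and frequency as examples of the summaries to be reported, and adds: "These summary statistics will guide the sample size calculation needed for the future definitive two arm cluster RCT". The article nowhere mentions an ICC, a between-practice variance, a design effect or an external source for any of them.

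**The concern.** In a cluster trial the number of practices is driven by how much outcomes vary between practices. The individually randomised sample size is multiplied by the design effect, 1 + (m - 1) × ICC for m patients per practice. An estimate that is to help choose the number of practices must therefore say something useful about the ICC. Information on the ICC comes mainly from the number of clusters and much less from the number of patients, and here there are six clusters, three per arm.

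The article calls the resulting estimates reliable without separating quantities that 60 patients can estimate (an SD) from those that six practices cannot (the ICC). A team designing the definitive trial could take that at face value. A pilot ICC of zero might then be read as evidence that clustering is negligible, and a chance high value as grounds for a far larger trial.

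**Working it through.** **Inputs from the article.** Practices k = 6, in 2 arms of 3; patients per practice m = 10 (Sample size calculations). Total 60 (Table 4: "Can 10 patients per practice (total n = 60) be recruited").

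**Assumed inputs.** The article gives no ICC, so 0.01, 0.02, 0.05 and 0.10 are tried. Practices are taken as equal in size, the outcome as continuous and roughly normal.

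**The plan's own figure.** 6 × 10 = 60, which agrees with Table 4. There is no alpha, power, SD or precision target behind it, so nothing further can be reproduced.

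**Degrees of freedom.** Between practices within arm: 6 - 2 = 4. Within practices: 6 × (10 - 1) = 54.

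**Exact interval for the ICC (one-way ANOVA estimator).**
- The observed variance ratio for an ICC estimate r is F = (1 + 9r)/(1 - r).
- The limits of the ratio are F/F(0.975; 4, 54) and F/F(0.025; 4, 54), with quantiles 3.034 and 0.1194.
- Each limit x converts back by ICC = (x - 1)/(x + 9).

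**Worked for r = 0.05.**
- F = 1.45/0.95 = 1.526.
- Lower: 1.526/3.034 = 0.503, so ICC = (0.503 - 1)/(0.503 + 9) = -0.052.
- Upper: 1.526/0.1194 = 12.78, so ICC = (12.78 - 1)/(12.78 + 9) = 0.541.
- Design effect at m = 10: 1.0 at the lower limit, once the negative value is truncated to zero, and 1 + 9 × 0.541 = 5.9 at the upper.

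**Chance that the estimate is zero or negative.** This is P(F(4, 54) ≤ (1 - ICC)/(1 + 9 × ICC)). For a true ICC of 0.05 the bound is 0.95/1.45 = 0.655 and the probability is 0.374.

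| Assumed ICC | 95% CI if this value is observed | Design effect at upper limit, m = 10 | P(estimate ≤ 0) if this is the true value |
|---|---|---|---|
| 0.01 | -0.07 to 0.45 | 5.1 | 53% |
| 0.02 | -0.06 to 0.48 | 5.3 | 49% |
| 0.05 | -0.05 to 0.54 | 5.9 | 37% |
| 0.10 | -0.03 to 0.63 | 6.6 | 25% |

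**Sensitivity, at an observed ICC of 0.05.**
- Ignoring arm (5 and 54 df): -0.05 to 0.46. The conclusion is the same.
- Five practices, which Table 4 still counts as a Go for retention: 5 - 2 = 3 and 5 × 9 = 45 df, upper limit 0.67.

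**Contrast with the SD.** On 54 df, ignoring clustering, the chi-square limits are 35.59 and 76.19. The 95% limits are √(54/76.19) = 0.84 and √(54/35.59) = 1.23 times the observed SD.

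**Scale.** At an ICC of 0.05 with ten patients per practice, the same method needs about 22 practices for a 95% CI half-width of 0.10 and about 71 for 0.05. This illustrates the gap; it is not a proposal to enlarge the pilot.

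**The case against.** The strongest reply is that a pilot needs no power calculation and that the article is candid: it says the number of practices is pragmatic, and it does not attach the word reliable to an ICC in particular. The pilot results are only to guide and inform the later calculation. All five progression criteria in Table 4 concern recruitment, retention or qualitative feasibility, so no stop/go decision turns on an ICC. All of this stands. Six practices is an acceptable pilot size, and nothing in its conduct is at fault.

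A reader might also infer two stronger points that the document does not support.

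- *That the Statistical analysis section leaves the ICC out.* Its list of summaries is introduced as examples, and the analysis plan is not shown. Means and SDs tabulated by practice, with practice sizes, would also be enough to compute an ANOVA ICC.
- *That the definitive trial would be sized with no design effect, or on the pilot ICC alone.* Objective 5 names the number of clusters explicitly, so clustering is in view, and nothing rules out external data.

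What the reply does not remove is the stated claim of reliability, tied to an objective that depends on between-practice variance. Adding an ICC to the analysis would not make the claim true, because its imprecision is set by the number of practices.

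**Conclusion.** The point holds as an overstatement of what the design can deliver. For between-practice variance, six practices of ten do not give reliable estimates. The upper 95% limit for the ICC is 0.45 to 0.63 across observed values of 0.01 to 0.10, and a zero or negative estimate has a 25% to 53% chance if the true value lies in that range. At an observed 0.05, the design effect is uncertain by a factor of almost six. For an SD the size is adequate for planning, at roughly -16% to +23%.

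The ICC values are assumptions, but the conclusion does not change over the range tried or with the treatment of arm. Unequal practice sizes or loss of a practice would be expected to widen the intervals. The matter affects what the pilot can conclude under objective 5. It does not affect participants, pilot conduct or the progression decision.

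**What to change.** - **Sample size calculations:** describe the estimates as preliminary, and say that six practices cannot estimate the ICC precisely. The expected interval can be given as in the table above.
- **Statistical analysis (or the analysis plan):** report the ICC for each main outcome, arm effect removed, with its 95% CI and as a descriptive result. State that the definitive design effect will rest mainly on ICCs from larger external primary-care data, with the pilot interval used only as a sensitivity range.
- **Objective 5:** no change is needed if it is read this way. The pilot still contributes SDs, recruitment, retention and the achieved practice sizes.

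The cost is a few sentences and a small addition to the analysis. The stated precision will look less favourable. No further practices or patients are required.
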